## Abstract

**Background:**

Acute myeloid leukemia (AML) is predominantly a disease of older patients with a poor long-term survival. Approval of the combination of venetoclax (VEN) with azacitidine (AZA) or decitabine (DAC) in the European Union in 2021 for the treatment of patients with newly diagnosed AML who are ineligible for induction chemotherapy has become the treatment backbone for older, medically non-fit AML patients. Based on in vitro priming of AML cells to all-*trans* retinoic acid (ATRA) by DAC, we had previously conducted a randomized phase II trial (DECIDER, AMLSG 14 − 09) in 200 elderly, non-fit AML patients on the effect of ATRA as add-on to DAC. Median overall survival (OS) was 8.2 months with ATRA versus 5.1 months without ATRA (hazard ratio, 0.65; 95% CI, 0.48 to 0.89; *P* = 0.006). Notably, ATRA did not add toxicity, the combination was active also in patients with adverse genetics, and prolonged time to treatment resistance. Investigating a triple combination of DAC, VEN and ATRA was a logical next step. This randomized double-blind phase III trial compares the efficacy of ATRA versus placebo as add-on to the backbone treatment (DAC and VEN) with respect to OS, objective best response, quality of life and safety. The accompanying translational research will contribute to identify molecular markers for drug efficacy and better tailoring epigenetic therapy.

**Methods:**

DECIDER-2 (AMLSG 32 − 21) is a prospective, randomized, double-blind, placebo-controlled, parallel group, multicenter trial. The primary study objective is to compare the efficacy of ATRA versus placebo as add-on to the backbone treatment (DAC and VEN) in terms of OS. The target population is adult AML patients unfit for standard induction chemotherapy. Patients are randomized (1:1) to receive backbone treatment in combination with either ATRA or placebo. Four interim safety analyses were planned with the involvement of the Data Monitoring Committee.

**Discussion:**

This trial investigates whether the in vitro cooperativity of DAC, VEN, and ATRA prolongs OS in unfit AML patients compared to placebo, offering a novel, low-toxicity triplet combination with a promising risk-benefit ratio.

**Clinical trial number:**

EU CT number: 2020-005495-36/2023-507461-26-00 (registered 18.11.2020); German clinical trials registry number: DRKS00023646 (registered 23.08.2022).

## Background

Acute myeloid leukemia (AML) is predominantly a disease of older patients, with a median age of > 65 years [1] who, however, are underrepresented in trials of standard induction chemotherapy. Ineligibility for intensive treatment is often due to reduced performance status, comorbidities etc [2].

Present treatment options for elderly AML patients unfit for standard chemotherapy are based on single-agent hypomethylating agents (HMAs) [3, 4], low- dose cytarabine, and more recently, HMA in combination with venetoclax (VEN) [5]. For unfit AML patients with mutations of the *IDH1/2* gene, specific inhibitors have been recently approved or integrated in clinical practice.

The research question arising from the medical problem addressed in the trial is whether an in vitro cooperativity between decitabine (DAC), VEN and ATRA can be confirmed in vivo, with extension of overall survival (OS) of AML patients receiving this 3-drug combination when compared to DAC, VEN and placebo. This triplet combination is novel and, since ATRA has very limited toxicities, promising regarding the risk-benefit ratio when administered to medically non-fit patients, in whom toxicity issues need to be particularly carefully considered during trial planning.

The impact of the results of this study is directly related to extension of OS of AML patients. Beyond AML treatment, a better understanding of in vivo cooperativity between HMAs and ATRA is potentially highly relevant also for other malignant disorders including solid tumors.

### Evidence and need of the trial

Our previous randomized clinical trial DECIDER (for DECItabine, DEacetylase inhibition, Retinoid) was conducted at 27 German trial centres and recruited 200 patients. The trial had a 2 × 2 design investigating the effects of ATRA and the HDAC inhibitor valproate as add-on to DAC. Patients were randomized to the following four treatment arms: DAC (*n* = 47), DAC+valproate (*n* = 57), DAC+ATRA (*n* = 46), and DAC+valproate+ATRA (*n* = 50).

DECIDER was a phase II study with primary endpoint objective best response (complete and partial remission) for a first efficacy assessment of valproate and ATRA add-on. For valproate, no effect was observed with respect to objective best response and overall survival. A beneficial effect of ATRA vs. no ATRA was present with respect to both best response and overall survival. The 1-year overall survival rates were 35% vs. 20%, median overall survival times were 8.2 vs. 5.1 months, hazard ratio (HR) = 0.65, 95% confidence interval (CI) [0.48,0.88], *p* = 0.006, ATRA vs. no ATRA, respectively [6].

The clinical benefit with ATRA was not at the expense of increased toxicity, in line with the safety concerns when combining drugs to treat elderly AML patients. Notably, patients receiving ATRA had a longer time to resistance development, and the survival benefit observed was similar in intermediate and adverse genetic risk groups. Following the positive results of the DECIDER trial, we planned to confirm this effect of ATRA in a placebo-controlled phase III clinical trial. Given the very impressive results in newly diagnosed AML patients receiving VEN in combination with AZA or DAC (see below), we hypothesized that when ATRA is combined with VEN and DAC in a “triplet”, response duration may be prolonged compared to the dual treatment with VEN and DAC, potentially via delay of development of secondary resistance.

In recent years, the treatment of AML patients ineligible for standard induction chemotherapy (IC), has made unexpected strides regarding the rapid and broad acceptance of the dual combination of a DNA hypomethylating agent (HMA) and the *BCL-2* inhibitor VEN. The VIALE-A phase III trial [5] demonstrated that the HMA azacitidine (AZA) plus VEN is superior to AZA monotherapy in most AML subgroups but not in *TP53* mutated patients [7]. HMA + VEN treatment has also been effective as „bridging“ approach in AML patients fit for the curative approach of allografting [8, 9]. This is not surprising considering the more favorable safety profile of HMA-based treatment compared to IC, as demonstrated in the randomized phase III Intergroup study AML21, coordinated by the EORTC Leukemia Group that compared an extended, 10-day DAC monotherapy induction to standard „7 + 3“ induction in AML patients aged 60 years and older [10, 11]. Very recently, DAC + VEN has been investigated, in a randomized phase II trial conducted by a Chinese consortium, as an alternative to intensive chemotherapy (idarubicin and cytarabine) in newly diagnosed AML patients aged 18–59 years, exhibiting a non-inferior response rate, but with fewer SAEs [12]. Indeed, the rapid and general adoption of an HMA-VEN de-escalation approach has prompted the initiation of multiple studies investigating triple combinations, e.g. HMA-VEN combined with inhibitors of *FLT3* [13], *IDH1/2* [14] or menin [15], a strategy that is similar to the approach we had taken in the DECIDER-2 trial as well as its predecessor DECIDER (DAC/valproic acid/ATRA).

Also in recent years, the potential of an HMA combined with ATRA has garnered renewed interest (reviewed by Geoffroy et al., 2021 [16]). In preclinical work we could show that in AML cell lines, DAC and ATRA had cooperative effects on induction of apoptosis and differentiation compared to either treatment alone; furthermore cells with mutated *TP53* treated with DAC+ATRA disclosed more effective derepression of transposable elements („viral mimicry“) than those with WT TP53 [17]. Similarly, the group of [name] (Hangzhou, China) showed that ATRA enhances the cytotoxic effects of DAC in AML blasts by activating the RARα-Nrf2 complex [18]. El Khawanky et al. (2025) [19] demonstrated that AZA efficacy, which is modulated by intrinsic RNA receptor signalling, can be restored by ATRA during acquired resistance. In a post-hoc subgroup analysis of patients from the DECIDER trial, we asked whether TP53-mutated patients also benefit from the HMA+ATRA combination; indeed, in patients with TP53 mutations the response rate in those receiving DAC+ATRA was higher when compared to those not receiving the ATRA add-on [20]. The survival benefit of TP53-mutated patients mediated by ATRA add-on was reduced, but not completely negated, warranting further investigation. Clinical evidence for efficacy of the HMA+ATRA combination was also generated in MDS: a randomized phase 2 trial in MDS-EB patients, coordinated by the Hangzhou group, also addressed the question of the benefit of ATRA add-on to DAC. The study resulted in a significantly higher response rate and progression-free survival in patients receiving the combination, compared to DAC monotherapy [21].

In conclusion, the evidence of preclinical and clinical studies generated in recent years supports the underlying hypothesis that a triplet of DAC, VEN and ATRA may be superior to DAC + VEN in AML patients of different risk groups, potentially including also TP53 mutated patients.

## Methods/design

### Study design and setting

This is a prospective, randomized, double-blind, placebo-controlled, parallel group, multicenter phase III trial. The primary objective of the trial is to compare the efficacy of all-*trans* retinoic acid (ATRA) versus placebo as add-on to the backbone treatment (DAC + VEN) in older and unfit AML patients with respect to OS. Secondary objectives are to compare ATRA *versus* placebo as add-on to the backbone treatment (DAC + VEN) with respect to objective best response, i.e. CR/CRi/MLFS/PR, CR with negative measurable residual disease (MRD), probability of survival with objective best response, quality of life (especially fatigue) and safety.

Trial sites are located in Aachen, Augsburg, Berlin-Buch, Berlin-Neukölln, Bochum, Bonn, Braunschweig, Düsseldorf, Eschweiler, Esslingen, Freiburg, Hagen, Halle, Hannover, Heidelberg, Jena, Karlsruhe, Kleve-Goch, Lahr, Lübeck, Lüdenscheid, Mannheim, Münster, Oldenburg, Rostock, Saarbrücken, Trier, Ulm and Villingen-Schwenningen.

The study received approval from the competent authority and ethics committees of the University of Freiburg as well as the respective local ethics committees and was successfully submitted to the CTIS. Patient’s written consent to participate in this clinical trial and translational research program was obtained prior to any study-specific procedures. The identifying number of the DECIDER-2 trial in the German clinical trials registry is DRKS00023646 and in EU clinical trials register 2020-005495-36/2023-507461-26-00.

### Study population

The target population of this trial represents patients older than 18 years with AML according to WHO (≥ 20% blasts in the peripheral blood or bone marrow) not qualifying for, or not consenting to, standard remission-induction chemotherapy or immediate allografting. Key inclusion criteria are: patient’s written informed consent; 18 years or older at time of informed consent; patients with primary or secondary AML according to WHO who are not expected to benefit from standard remission-induction chemotherapy; <25.000 leukocytes/µl and performance status ECOG 0, 1, 2. Key exclusion criteria are: Acute promyelocytic leukemia (APL), AML of FAB subtype M3; previous remission-induction chemotherapy for MDS or AML; previous allogeneic stem cell transplantation; previous treatment with DAC, 5-azacytidine, VPA or other DNA-hypomethylating agents, ATRA, venetoclax and other Bcl-2 inhibitors; “low-dose” chemotherapy (e.g. hydroxyurea, cytarabine (Ara-C), melphalan etc.) within four weeks prior to the first ATRA/placebo administration, except for cytoreduction of leukocytosis ≥ 25.000/µl with hydroxyurea or Ara-C as prescribed by the study protocol. Further exclusion criteria are related to general medical conditions or contraindications to administration of investigational product according to Summary of Product Characteristics.

### Study treatment and procedures

Study treatment in the two study arms (Fig. 1) is as follows. Experimental Arm: backbone treatment (consisting of intravenous DAC 20 mg/m² over 1 h, 5 days [total dose 100 mg/m²], repeated every 4 weeks, and VEN *per os* (p.o.) ramp-up (during posaconazole prophylaxis, which is strongly recommended): 10 mg on day 1, 20 mg on day 2, 50 mg on day 3 and 100 mg from day 4 until day 14 or 21/28 depending on blast clearance), and ATRA p.o. 45 mg/m^2^ days 6–28. Control Arm: backbone treatment and placebo p.o. corresponding to ATRA dose.

**Fig. 1 Fig1:**
[figure not shown]
Trial Flow. *If WBC ≥ 25.000/µl: Hydroxyurea (HU) or Ara-C until WBC < 25.000/µl. ATRA = all-*trans* retinoic acid; BM = bone marrow; CR = complete remission; CRi = complete remission with incomplete count recovery; DAC = decitabine; DMC = data monitoring committee; MLFS = morphologic leukemia-free state; pB = peripheral blood; PR = partial remission; VEN = venetoclax; WBC = white blood cell count; WHO = world health organization

Treatment cycles (backbone and study medication) are repeated until relapse/progression, hematopoietic cell transplantation (HCT), death or unacceptable toxicity (whichever occurs first). Response assessment is performed in cycle 1, at the end of the cycles 2, 4, 6, and 13 and in case of suspected relapse/progression. Study visits are carried out at least once a month during the treatment and every three months after treatment discontinuation until 12 months after randomization of the last patient.

### Study endpoints

The primary endpoint is the OS defined as time from the date of randomization to the date of death from any cause. Secondary endpoints for the evaluation of efficacy are the following: (1) objective best response (OBR) defined as CR, CRi, morphologic leukemia-free state (MLFS) or partial remission (PR) assessed after cycles 1, 2, 4, 6, and 13. Patients are counted as objective responders if they achieve a CR, CRi, MLFS or PR. All other patients are counted as non-responders. The determination of CR, CRi, MLFS or PR is performed according to the standard criteria [22]; (2) response defined as CR with negative measurable residual disease (CR_MRD-_) assessed after cycles 2, 4, and 6; (3) survival probability after attainment of objective best response (CR, CRi, MLFS or PR) defined as time from objective best response to the date of death from any cause; (4) quality of life (QOL) of the patients using the EORTC QLQ-C30 Quality of Life Questionnaire, and FACIT Fatigue Scale. Further secondary endpoint for evaluation of the treatments is safety and toxicity, which are evaluated by means of adverse events (AEs) occurring from the first administration until 30 days after the last administration of study medication or first day of hospitalization for HCT or until start date of any tumor-specific treatment in case of relapse/progression (whichever occurs first) and serious AEs related to the study medication as per investigator’s judgment reported until end of the study.

### Sample size

Sample size calculation is based on the primary endpoint OS. The study should have a power of 80% to demonstrate superiority of ATRA vs. placebo with respect to OS at one-sided level alpha of 2.5% under the assumption of a hazard ratio of 0.67. This requires the observation of 191 deaths. A hazard ratio of 0.67 would correspond e.g. to a median OS time of 12 months vs. 8 months. The median OS time of 286 patients treated with AZA plus VEN 400 mg in the VIALE-A trial by DiNardo et al. (2020) [5] was reported as 14.7 months, in the control group of 145 patients treated with AZA plus placebo it was reported as 9.6 months (hazard ratio 0.66, 95% confidence interval [0.52, 0.85], *p* < 0.001 of VEN vs. placebo). In the DECIDER trial, the median OS time of 96 patients treated with DAC+ATRA (+/- valproate) was 8.2 months, and of 104 patients treated with DAC (+/-valproate) was 5.1 months, with a hazard ratio of 0.65, 95% confidence interval [0.48,0.88], *p* = 0.006 of ATRA vs. no ATRA [6].

Thus, the assumption of median OS times of 12 vs. 8 months for the planned trial seems to be realistic. Under this assumption, and a planned recruitment period of 3 years and an additional follow-up period of 1 year, it is necessary to include 230 patients (nQuery Advisor 7.0). If longer median OS times were observed (e.g. 15 vs. 10 months, also corresponding to a hazard ratio of 0.67), the follow-up period had to be extended to 1.5 years, in order to observe the required number of 191 deaths with the same number of included patients. To account for the possibility of up to 10% of the patients with incomplete follow-up, 230/0.9 = 256 patients will be randomized in total (ratio 1:1).

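### OS follow-up is fixed at 12 months after the last randomisation, yet 191 deaths are required and control medians above 10 months are not worked through

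*Protocol article*

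**What the plan says.** The control arm receives decitabine plus venetoclax plus placebo. Study design and setting compares ATRA "versus placebo as add-on to the backbone treatment (DAC + VEN) in older and unfit AML patients with respect to OS".

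The Sample size section of the protocol article sets 80% power for "superiority of ATRA vs. placebo with respect to OS at one-sided level alpha of 2.5% under the assumption of a hazard ratio of 0.67", and adds: "This requires the observation of 191 deaths". It illustrates the effect with medians: "A hazard ratio of 0.67 would correspond e.g. to a median OS time of 12 months vs. 8 months".

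It then cites two sources:

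- "The median OS time of 286 patients treated with AZA plus VEN 400 mg in the VIALE-A trial" "was reported as 14.7 months, in the control group of 145 patients treated with AZA plus placebo it was reported as 9.6 months", with a venetoclax hazard ratio of 0.66.
- The predecessor trial (decitabine with or without valproate, no venetoclax): 8.2 months with ATRA and 5.1 months without.

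It concludes: "Thus, the assumption of median OS times of 12 vs. 8 months for the planned trial seems to be realistic". On that basis 230 patients suffice with 3 years of recruitment and 1 year of follow-up, and 256 are randomised to allow for 10% incomplete follow-up. If survival proves longer, for example 15 vs 10 months, follow-up is to be lengthened to 1.5 years so that 191 deaths are still reached with the same number of patients.

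Study treatment and procedures, in the text after Figure 1, has visits continue every three months after treatment stops and ends them 12 months after the last patient is randomised. It mentions neither an extension nor a death count.

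**The concern.** There are two weaknesses, and they compound each other.

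First, the only median cited for a hypomethylating agent plus venetoclax is 14.7 months. The plan works through control medians of 8 and 10 months and nothing higher. It gives no reason for preferring 8 to 14.7, so the word that introduces its conclusion is not backed by a stated step.

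Second, the requirement is a number of deaths, but the follow-up section stops on a calendar date. The two agree at the planned 12 vs 8 months. They part as soon as survival is longer, which the Sample size section itself treats as possible.

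If survival is longer and the calendar date is kept, a confirmatory OS trial described as having 80% power would be analysed with fewer deaths and less power. Type I error is not affected.

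**Working it through.** **Inputs from the article.** One-sided alpha 0.025; power 80%; 1:1 allocation; 191 deaths; 230 patients, or 256 randomised; 36 months of accrual; follow-up 12 months, or 18 in the fallback. Actual accrual (Study status): 233 randomised from October 2022 to 16 June 2026, about 44.5 months.

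**Assumptions of this check.** Exponential survival, uniform accrual, hazard ratio 2/3 (12 vs 8 months exactly).

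**Formulas.**

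- Deaths required: d = 4(1.960 + 0.842)² / (ln HR)².
- Probability of death under observation, with hazard λ = ln 2 / median, accrual R and further follow-up F: P = 1 − [exp(−λF) − exp(−λ(R+F))] / (λR).
- Expected deaths: N times the mean of P over the two arms.
- Power: Φ(√d/2 × ln 1.5 − 1.96), where ln 1.5 = 0.4055.

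**The plan's own figures reproduce.**

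- Hazard ratio 2/3 gives d = 191 (a rounded 0.67 gives 196).
- 12 vs 8 months, R = 36, F = 12: P = 0.892 and 0.790, mean 0.841; × 230 = 193 deaths.
- 15 vs 10 months, R = 36, F = 18: 193 to 194 deaths from 230.
- 230/0.9 = 256.

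**Control median 14.7 months** (ATRA arm 14.7 × 1.5 = 22.05), R = 36, F = 12:

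- Control: λ = 0.04715, P = 1 − (0.568 − 0.104)/1.698 = 0.727.
- ATRA: λ = 0.03144, P = 1 − (0.686 − 0.221)/1.132 = 0.589.
- Mean 0.658; × 230 = 151 deaths. Power = Φ(√151.4/2 × 0.4055 − 1.96) = 70%.

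**Range.** The lower figure uses 230 patients (the 26 allowed for as incomplete contribute no deaths). The upper uses all 256 with no loss. The truth lies between. At the observed rate, 233/44.5 = 5.24 per month, 256 patients take about 49 months, so 48-month accrual is close to actual.

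| Control median | Follow-up | 36-month accrual: deaths (power) | 48-month accrual: deaths (power) |
|---|---|---|---|
| 12 | 12 months | 167–185 (74–79%) | 178–198 (77–81%) |
| 14.7 | 12 months | 151–168 (70–75%) | 163–182 (74–78%) |
| 14.7 | 18 months | 167–186 (75–79%) | 177–197 (77–81%) |

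**Follow-up needed for 191 deaths at 14.7 months.** With 36-month accrual, about 31 months (230 patients) or 20 months (256). With 48-month accrual and 230 patients, about 26 months.

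**Where the 8 and 12 months could come from.** Dividing the predecessor trial's medians by the venetoclax hazard ratio gives 5.1/0.66 = 7.7 and 8.2/0.66 = 12.4, close to both planned values. The article does not show this step.

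**The case against.** The strongest defence is that the assumption has a visible basis. Both planned medians follow from figures in the same section, as shown above. The predecessor trial used this trial's hypomethylating agent, and its arm without ATRA had a median of 5.1 months, against 9.6 months for azacitidine alone in the cited phase III trial. A planned control below 9.6 months is therefore no anomaly. This stands.

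A reader might go further and infer that 14.7 months is the true control median, so that 8 months is simply wrong. The article does not support that. The figure comes from azacitidine plus venetoclax 400 mg in another population, and the gap between 5.1 and 9.6 months shows that absolute medians may not transfer between these trials.

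Next, the Sample size section already provides for longer follow-up, and its 15 vs 10 months is given as an example, not a limit. The 191 deaths do not depend on the medians, so longer survival mainly costs calendar time. This also stands, but the follow-up section does not carry the provision through.

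Last, slower accrual and the 256 patients help. With 48-month accrual, no loss and 18 months of follow-up, even 14.7 months gives 197 deaths. So it would be too strong to say that 191 deaths are reached only at the pessimistic end of the cited evidence. A complete protocol may also hold fuller timing rules, but the two sections shown still need to agree.

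**Conclusion.** The point holds in a limited form. The plan's arithmetic is sound, and its planned medians are defensible though unexplained. What is fixed badly is the end of follow-up: a calendar limit in one section against a required death count in another, with no scenario above a control median of 10 months.

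If the control median were 14.7 months, the 12-month limit would miss 191 deaths in every case examined, by 9 (191 − 182) to 40 (191 − 151). An 18-month limit would miss by 5 (191 − 186) to 24 (191 − 167), except with slow accrual and almost no loss. At a control median of 12 months, the 12-month limit misses by up to 24 (191 − 167) and is met only with slow accrual and almost no loss.

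These sizes rest on exponential survival, uniform accrual and a hazard ratio of 2/3. They describe what would happen at a given median, not what this trial's median is. They should not be read as showing that the trial is underpowered or needs more patients.

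**What to change.** 1. Reconcile Study treatment and procedures with Sample size: end OS follow-up, and trigger the final analysis, when 191 deaths have been observed, in place of a fixed 12 months after the last randomisation.
2. Check the pooled, blinded death count now. It needs no unblinding and has no alpha cost, and it shows which scenario applies while follow-up can still be extended.
3. Restate expected deaths, power and the follow-up needed for 191 deaths at control medians of 8, 10, 12 and 14.7 months, using actual accrual and showing results both with and without the 10% loss.
4. Replace the claim of realism with the stated basis for 8 months; if it is the scaling of the predecessor medians by the venetoclax hazard ratio, say so. Describe 14.7 months as the nearest cited benchmark, not as this control arm's median.

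Do not add patients; time under observation supplies the missing deaths. The cost is a recalculation and a change of text, plus either a later read-out with longer visits or, if a fixed date is kept, a lower stated power.
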